## Abstract

**Background:**

Incisional hernia is a common complication after kidney transplantation with an incidence of 1.6–18%. Concerning non-transplant patients, a recently published meta-analysis describes a reduction of the incidence of incisional hernia of up to 85% due to prophylactic mesh replacement in elective, midline laparotomy. The aim of our study is to show a reduction of the incidence of incisional hernia after kidney transplantation with minimal risk for complication.

**Methods/design:**

This is a blinded, randomized controlled trial comparing time to incisional hernia over a period of 24 months between patients undergoing kidney transplantation and standardized abdominal closure with or without prophylactic placement of ProGrip™ (Medtronic, Fridley, MN, USA) mesh in an onlay position. As we believe that the mesh intervention is superior to the standard procedure in reducing the incidence of hernia, this is a superiority trial.

**Discussion:**

The high risk for developing incisional hernia following kidney transplantation might be reduced by prophylactic mesh placement. ProGrip™ mesh features polylactic acid (PLA) microgrips that provide immediate, strong and uniform fixation. The use of this mesh combines the effectiveness demonstrated by the macropore propylene meshes in the treatment of incisional hernias, a high simplicity of use provided by its capacity for self-fixation that does not increase significantly surgery time, and safety.

**Trial registration:**

ClinicalTrials.gov NCT04794582. Registered on 08 March 2021. Protocol version 2.0. (02–18-2021).

## Administrative information

**Table Taba:** 

Title {1}	Prevention of Incisional Hernia after Kidney Transplantation: Study Protocol for a Randomized Controlled Trial
Trial registration {2a and 2b}	ClinicalTrials.gov. ID: NCT04794582. Registered on 08 March 2021. Protocol version 2.0. (02–18-2021) ClinicalTrials.gov collects all (20 out of 20) items from the World Health Organization Trial Registration Data Set
Protocol version {3}	Registered on 08 March 2021. Protocol version 2.0. (02–18-2021)
Funding {4}	Medtronic (Fridley, Minnesota. USA) will provide all necessary material (ProGrip™ meshes) and financial support for translation and language editing services

## Introduction

### Background and rationale {6a}

#### Background

Incisional hernia is a common complication after kidney transplantation with an incidence of 1.6–18.0% [1–4]. Several studies have identified multiple risk factors for the development of post-transplant incisional hernia that can be grouped into patient and donor factors, factors related to immunosuppression and factors related to the location and type of surgical incision [1–7]. In 2018, Simson et al. published a systematic review of the existing literature that highlights the limited scientific evidence that is mainly constituted by the review of case series. The risk factors identified were body mass index (BMI) > 30, age > 50 years, cadaveric donor transplantation and the need for reoperation [2]. The essential immunosuppressive therapy after transplantation has a negative impact on wound healing and leads to the formation of dysfunctional scar tissue. In the case of immunosuppressive medication, nucleotide synthesis inhibitors such as mycophenolate and mammalian target of rapamycin (m-TOR) inhibitors such as sirolimus have been associated with a higher incidence of incisional hernia [8].

Artificial mesh is commonly used in ventral incisional hernia repair as described in the literature, but there is yet no scientific paper on the use of prophylactic mesh placement at the time of transplantation. The main reason, therefore, is that immunosuppressive therapy and artificial mesh implantation seem to be contradictory due an increased risk of complications. Concerning non-transplant patients, a recently published meta-analysis by Borab et al. describes a reduction of the incidence of incisional hernia of up to 85% due to prophylactic mesh replacement in elective, midline laparotomy [9].

Several clinical trials with ProGrip™ meshes have been registered at international clinical trials registries. Medtronic ProGrip® is a macropore (1.1–1.7 mm) polypropylene self-fixing monofilament mesh that features polylactic acid (PLA) microgrips that act providing immediate, strong and uniform fixation, weighing 82 g/m2 before PLA resorption and 41 g/m2 after resorption (low density). The use of this mesh combines the effectiveness demonstrated by the macropore propylene meshes in the treatment of incisional hernias, a high simplicity of use provided by its capacity for self-fixation in relation with the so-called absorbable microgrips of PLA that adhere quickly and easily to the underlying tissue and safety. This mesh has demonstrated its usefulness and safety for the prophylaxis of eventration in patients with other types of lateral incisions [10].

Although the incidence of incisional hernia in lateral laparotomies is lower than that of median laparotomy, their treatment is considered to be more complex, especially in the context of kidney transplantation in relation to surgical incision lateral position to the sheath of the rectus abdominis muscle, graft presence in the iliac fossa, difficult fixation for prostheses because of the proximity to the inguinal area, costal margin and iliac bones and immunosuppression [3, 5–7, 11–14]. In the present study, we used the definition of eventration or incisional hernia accepted by the European Hernia Society: “Eventration or incisional hernia is any defect in the abdominal wall with or without associated bulging in the area of a surgical scar perceptible or palpable by physical examination or imaging tests” [15].

### Objectives {7}

#### Primary end-point

To determine the efficacy of mesh reinforcement in laparotomy closure in renal transplantation compared to standardized abdominal closure, as measured by reduction in the incidence of incisional hernia at 2 years post-transplantation.

#### Secondary end-points

To determine the safety of mesh reinforcement in laparotomy closure in renal transplantation as measured by determining the incidence of surgical wound complications: number of seromas, number of surgical wound infections, incidence and severity of acute and chronic pain, and need for mesh removal.

To determine the efficacy of mesh reinforcement in laparotomy closure in renal transplantation measured by radiological diagnosis (CT) of incisional hernia at 2 years post-transplantation.

To determine the incidence of surgery for incisional hernia in post-renal transplantation.

### Trial design {8}

#### Aim of the study

The aim of our study is to show a reduction in the incidence of incisional hernia after kidney transplantation with minimal risks for complications. We believe that the mesh intervention is superior to the standard procedure in reducing the incidence of hernia; therefore, it is a superiority trial in the form of a blinded randomized clinical trial.

## Methods: participants, interventions and outcomes

### Study setting {9}

Unicentric study carried out at an academic hospital. The source of information will be constituted by the Electronic Clinical History of the Hospital Centre in what refers to the clinical notes of the physicians responsible for the care of the patients, laboratory data and radiological explorations carried out in the follow-up of the patients.

### Eligibility criteria {10}

The study population consists of patients > 18 years of age who received a first kidney transplant.

Inclusion criteria: ≥ 18 yearsCandidate for first renal transplantGives informed consent

Exclusion criteria:Patient receiving a second or subsequent renal transplantationDoes not give informed consent

### Who will take informed consent? {26a}

Informed consent for the study will be obtained prospectively at the time of the visit corresponding to the pre-transplant evaluation by the Principal Investigator or, as authorized surrogates, any member of the Kidney Transplant Surgery Team after complete explanation of study conditions to potential recipients of a first kidney transplantation. For patients previously included in the kidney transplant waiting list, informed consent will be obtained at the time the patient is called as a potential renal transplant recipient, after revision of inclusion and exclusion criteria. When a patient signs the written informed consent, they are enrolled in the study.

## Interventions

### Explanation for the choice of comparators {6b}

This is a blinded randomized controlled trial comparing the incidence of incisional hernia between patients undergoing kidney transplantation with or without prophylactic mesh placement. Incisional hernia is a common complication after kidney transplantation with an incidence of 1.6–18.0%. Prophylactic mesh is commonly used in ventral incisional hernia repair as described in the literature, but there is yet no scientific paper on the use of prophylactic mesh placement at the time of transplantation.

The status of the abdominal wall and the existence of risk factors for development of hernia after kidney transplantation will be evaluated. The patients will be randomly allocated to either the standard of care or the intervention group.

### Intervention description {11a}

#### Surgical technique

The transplant team has been specifically trained by the General and Visceral Surgery Department and has unified the surgical approach and abdominal wall closure technique with only minor variations among its members. The surgical approach is performed through a paramedian incision, pararectal incision or field hockey stick incision which have in common that all of them use the semilunar ligament on the lateral border of the rectus abdominis muscle to gain access to the retroperitoneal space in the iliac fossa.

#### Abdominal-wall closure technique — intervention group

In the intervention group, once the closure in 2 muscle-aponeurotic planes with continuous synthetic suture described in the previous paragraph has been completed, the closure will be completed by placing the ProGrip® macroporous polypropylene monofilament mesh in supra-aponeurotic position using the surface with PLA microgrips, which act as Velcro, in direct contact with the superficial aponeurotic plane constituted by the aponeuroses of the greater oblique muscle and the crescentic line of the anterior rectus abdominis muscle. The PLA microgrips provide immediate fixation, making additional fixation with stitches unnecessary, which makes the technique very easy to use and systematize among the different surgeons of the transplant team. The procedure is completed with the placement of a low-calibre round Jackson-Pratt subcutaneous drain (10F) connected to a vacuum system.

The mesh implant technique is based on a PRIMA multicentre, double-blind, randomized controlled trial which shows that only reinforcement mesh decreases incisional hernia without increasing complication rates with respect to primary closure [16].

#### Abdominal-wall closure technique — control group

In the control group, the surgical team will proceed according to standard clinical practice with closure using the technique in 2 muscle-aponeurotic planes with very long-term (3 months) absorbable synthetic continuous suture of poly(4-hydroxybutyrate), monofilament, elastic (Monomax® USP 0) according to the small-bites technique. In order to achieve masking of the participating subject, a small-bore (10F) Jackson-Pratt drain connected to a vacuum system will be placed in the subcutaneous space at the end of the procedure in a manner similar to the intervention group. In both treatment groups, the subcutaneous drain will be removed on post-transplant day 2 or 3. Placement of this drain is not associated with increased patient risk.

### Criteria for discontinuing or modifying allocated interventions {11b}

The patient will be able to revoke his/her consent at any time until surgery. The kidney transplant surgeon will be able to modify intervention allocation if the local or patient general condition does not advise to carry out the assigned abdominal-wall closure technique. No other modification of allocated intervention will be possible once abdominal-wall closure is completed.

This modification must be adequately justified and will be taken into account during data analysis (intention-to-treat and per-protocol analysis).

### Strategies to improve adherence to interventions {11c}

Not applicable. The patient will be blinded for intervention. Kidney transplant patients’ adherence to follow-up is usually high.

### Relevant concomitant care permitted or prohibited during the trial {11d}

Not applicable. There are no concomitant care or prohibited interventions during patients’ follow-up. Post-transplant ultrasound kidney monitoring and biopsy are possible in presence of a mesh.

### Provisions for post-trial care {30}

Not applicable. Polypropylene meshes have demonstrated their utility and safety in incisional hernia prophylaxis. In the context of kidney transplantation, although experience is scarce, no association was identified between the use of prophylactic mesh and the occurrence of surgical wound infections. Because of the previous reasons and after the Ethical Committee evaluation, it was not considered necessary to take out specific liability insurance for the trial.

### Outcomes {12}

First outcomeIncidence of incisional hernia at 2 years post-transplantation. Categorical variables (incisional hernia proportion in each group) will be described by absolute and relative frequencies. In addition, differences between groups will be calculated by chi-square test. Time to incisional hernia onset will be described by Kaplan–Meier survival analysis and compared by log-rank test.

Secondary outcomesSafety of mesh reinforcement in laparotomy closure in renal transplantation measured by determining the incidence of surgical wound complications: number of seromas, number of surgical wound infections, incidence and severity of acute and chronic pain, and need for mesh removal. Categorical variables (incisional hernia proportion in each group) will be described by absolute and relative frequencies. In addition, differences between groups will be calculated by chi-square test.Incidence of incisional hernia at 2 years post-transplantation by radiological diagnosis (CT). Categorical variables (incisional hernia proportion in each group) will be described by absolute and relative frequencies. In addition, differences between groups will be calculated by chi-square test. Time to incisional hernia onset will be described by Kaplan–Meier survival analysis and compared by log-rank test.Incidence of surgery for incisional hernia in post-renal transplantation. Categorical variables (incisional hernia surgery proportion in each group) will be described by absolute and relative frequencies. In addition, differences between groups will be calculated by chi-square test. Time to incisional hernia onset will be described by Kaplan–Meier survival analysis and compared by log-rank test.

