### Sample size {14}

For the primary endpoint (incisional hernia at 24 months), assuming a proportion in the control group of 20%^1^ and a proportion of 5% in the intervention group (prophylactic mesh reinforcement placement), with an alpha level of 0.05 and power of 80%, the sample size per group was calculated at 76 patients.

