## Statistical methods

### Statistical methods for primary and secondary outcomes {20a}

The primary analysis will be by intention-to-treat (ITT), including all randomized patients who have undergone renal transplantation. A per-protocol analysis will also be performed with all patients. Demographic and clinical parameters will be described by mean and standard deviation or median and its confidence interval for continuous variables depending on the normal or non-normal distribution of the sample. Categorical variables will be described by absolute and relative frequencies. In addition, differences between groups will be calculated using Student’s *t*-test or Mann–Whitney *U* test depending on the sample distribution and the chi-square test. Time to incisional hernia onset will be described by Kaplan–Meier survival analysis and compared by log-rank test. The analysis will include stratification by the variable “obesity”. A *p*-value < 0.05 will be considered statistically significant. We performed our analyses with Stata v16.1 (StataCorp, TX, USA).

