### Methods in analysis to handle protocol non-adherence and any statistical methods to handle missing data {20c}

Methods to handle missing data:

During the data collection stage by monitoring data quality. During the analysis stage before estimation of statistics.

For Missing Completely at Random (MCAR) and Missing at Random (MAR) data losses, the multiple imputation technique will be used, whereas for Missing Not At Random (MNAR) we will opt for pairwise.

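### Kaplan–Meier for time to hernia censors deaths, so the 24-month value read from the curve slightly overstates hernia incidence; a cumulative incidence function would not

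*Protocol article*

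**What the plan says.** Outcomes {12} defines the first outcome as "Incidence of incisional hernia at 2 years post-transplantation" and reports it in two ways. The first is a crude proportion per arm, for which "differences between groups will be calculated by chi-square test". The second is a curve: "Time to incisional hernia onset will be described by Kaplan–Meier survival analysis and compared by log-rank test". The curve and log-rank test are repeated there for CT-diagnosed hernia and for hernia surgery, and again in Statistical methods {20a}.

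The intention-to-treat set in {20a} is defined as "including all randomized patients who have undergone renal transplantation", so a patient who dies later in follow-up stays in it.

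The missing-data section {20c} has two rules. One is "For Missing Completely at Random (MCAR) and Missing at Random (MAR) data losses, the multiple imputation technique will be used". The other is "whereas for Missing Not At Random (MNAR) we will opt for pairwise". Neither mentions death. The article names no competing event and no censoring rule.

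**The concern.** A transplant recipient who dies without a hernia can no longer develop one. Kaplan–Meier with hernia as the only event removes that patient as censored, which amounts to assuming the same future hernia risk as in those still under observation. The complement of the curve is then the risk in a hypothetical population without deaths, not the share of transplanted patients who get a hernia, and the outcome is worded as the latter.

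What is at stake is the size of the reported incidence in each arm and of the absolute reduction from mesh, not the hypothesis test. There is also a matter of consistency. The same 24-month quantity is reported as a crude proportion and can be read from the curve. If deaths count as hernia-free in one and are censored in the other, the two figures differ by construction.

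**Working it through.** **Inputs from the article.**
- Sample size {14}: "assuming a proportion in the control group of 20" per cent and "a proportion of 5% in the intervention group" at 24 months, two-sided 5% level (the article does not state sidedness), 80% power, 76 per group.
- Participant timeline {13}: in the centre's own cohort the median time to hernia was 17.1 months, with quartiles 2.6 and 23 months.

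**Assumed.** The article gives no mortality. I take d = 2%, 5% or 10% dead by 24 months (about 3, 8 or 15 of 152), equal in both arms and independent of hernia.

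**The plan's own figure.** With pooled variance under the null and no continuity correction, n = [1.96·√(2·0.125·0.875) + 0.8416·√(0.2·0.8 + 0.05·0.95)]² / 0.15² = 75.1, rounded up to 76. The stated figure reproduces.

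**Check 1: constant hazards over two years.** Let p be the value of one minus Kaplan–Meier at 24 months.
- Hernia hazard λh = −ln(1−p)/2, which is 0.1116 per year for 20% and 0.0256 for 5%.
- Death hazard λd = −ln(1−d)/2, which is 0.0101, 0.0256 and 0.0527 for d = 2%, 5% and 10%.
- Actual cumulative incidence = λh/(λh+λd) × [1 − exp(−2(λh+λd))].

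**Check 2: the centre's hernia timing.** Hernia onset is spread piecewise linearly, a quarter in each of 0–2.6, 2.6–17.1, 17.1–23 and 23–24 months. Survival is G(t) = (1−d)^(t/24). Actual cumulative incidence = p × mean of G over the onset distribution. That mean is 0.9886, 0.9714 and 0.9425 for the three values of d.

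| Deaths by 24 months | Curve shows 20%: actual (check 1 / check 2) | Curve shows 5%: actual (check 1 / check 2) | Difference of 15 points: actual (check 1 / check 2) |
|---|---|---|---|
| 2% | 19.81 / 19.77 | 4.95 / 4.94 | 14.86 / 14.83 |
| 5% | 19.51 / 19.43 | 4.88 / 4.86 | 14.64 / 14.57 |
| 10% | 19.02 / 18.85 | 4.75 / 4.71 | 14.27 / 14.14 |

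The overstatement is therefore 0.19 to 1.15 points at 20%, 0.05 to 0.29 points at 5%, and 0.14 to 0.86 points on the difference. In relative terms check 2 gives 1/0.9886 − 1 = 1.2% to 1/0.9425 − 1 = 6.1%. Late hernia timing adds little: 19.02 − 18.85 = 0.17 points at most. The risk ratio stays at 0.25 in both checks.

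**How far the two reports of the same outcome could part.** Take the control arm at 10% deaths under constant hazards. The curve shows 20%. A crude proportion that counts deaths without hernia as hernia-free shows 19.0%. If those patients were instead dropped, the calculation is as follows. The share dying without hernia is λd/(λh+λd) × [1 − 0.8·0.9] = 0.3207 × 0.28 = 8.98%, and the crude proportion becomes 19.02/(100 − 8.98) = 20.9%. The article does not say which of these applies.

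**The case against.** The strongest reply is that the main incidence measure is the crude proportion, not the curve. Its denominator is all randomized patients who received a transplant. Read plainly, a patient followed to death without a hernia is a non-case in it, and that proportion is unbiased. The sentence on Kaplan–Meier describes time to onset and does not say that the 24-month incidence will be read from it. Censoring rules are also commonly left to a statistical analysis plan, which is not at hand. Finally, the effect is small and depends on mortality figures that the article does not give.

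Much of this stands. A reader might infer from the missing-data section that deaths are treated as missing, so that a dead patient is given an imputed hernia status or dropped, and that both reports of the outcome then overstate incidence. The text does not support that. The section never classes death as a data loss, and the crude proportion can be read as keeping deaths as hernia-free.

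The choice of Kaplan–Meier with hernia as the only event does not fall away. The article fixes that method, in two sections and for three outcomes. An analysis plan that kept it would carry the same bias whatever detail it added.

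**Conclusion.** The point holds for the curve and is minor. The 24-month value read from it overstates hernia incidence by about 0.2 to 1.15 points where it shows 20%, by about 0.05 to 0.3 points where it shows 5%, and by up to about 0.9 points on the 15-point difference. These sizes rest on assumed two-year mortality of 2% to 10%, equal in the arms and independent of hernia. The direction does not depend on the figure chosen.

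Bias in the crude proportion is possible but not established. The log-rank test remains a valid comparison of cause-specific hernia hazards. Nothing here shows that the trial's conclusion would change. Only unequal mortality between the arms would shift the contrast itself, which is a reason to report deaths by arm.

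**What to change.** In Outcomes {12} and Statistical methods {20a}, describe time to hernia by the cumulative incidence function (Aalen–Johansen) with death without hernia as a competing event. Do the same for CT-diagnosed hernia and hernia surgery. Keep the log-rank test and label it a comparison of cause-specific hernia hazards.

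In the missing-data section {20c}, state that hernia status is not imputed after death and that a patient who died without a hernia stays in the denominator of the 24-month proportion as no hernia. Show deaths by arm alongside.

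The cost is a few sentences, date of death as a data item, and a competing-risk routine in the analysis. The chi-square test, the sample size and trial conduct need no change. The downside is a slightly lower reported incidence and a little more analysis work.

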Muysoms et al. in 2017 conducted the review of all published articles on the use of prophylactic mesh reinforcement (excluding studies on para-stomal hernia prevention) with no restrictions on the type of study or qualitative analysis [20]. All data on the degree of contamination and number of wound and/or mesh infections were extracted and analysed. The use of prophylactic mesh reinforcement to prevent incisional hernias had been published in the literature in 1,759 patients, with an overall wound infection rate of 12% and a mesh infection rate of 0.6%. The procedure, it was concluded, could be considered safe and effective in both clean and clean-contaminated surgery. Regarding the position of the prophylactic mesh, both supraaponeurotic and retromuscular positions have been used. Both seem equally safe and effective and probably the position of the mesh will depend on the preference of each surgeon. However, to identify in which group of at-risk patient’s prophylactic mesh should be recommended, the authors conclude that further studies are needed. In contrast, the existing literature on the prophylactic use of mesh for wall closure in the context of renal transplantation is very scarce [22–25]. Of the 3 articles identified, 2 of them refer to their use for the prevention or treatment of compartment syndrome in renal transplantation [22, 23]. Beasley et al. use a propylene mesh as a bridge between the posterior fascial planes with the aim of achieving enlargement of the closure and reduction of the pressure exerted on the graft; in this way, the graft was saved in 15 of the 17 cases used, the associated complications being minor in all cases with the occurrence of 5 cases of seroma and 1 lymphocele. In 2015, Wood et al. publish the use of prophylactic polypropylene mesh in the prophylaxis of compartment syndrome in renal transplantation. Of a total of 134 patients in whom mesh was implanted only 1.5% developed surgical wound infection, a result similar to that of the non-implanted population (1.3%). The mesh removal rate was 6% (8/134). Only the article by Michalski et al. referred to the use of mesh for prophylaxis of early surgical wound complications [22]. A reduction, although not significant, of surgical wound complications was identified in the group in which closure reinforced with Vycril™ (polyglactin 910) resorbable mesh was used. No association was identified between the use of prophylactic mesh and the occurrence of surgical wound infections, a potential complication feared by the use of mesh in the context of immunosuppression and transplantation.

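### Repeated boilerplate under the secondary outcomes puts mesh removal under a between-arm test, times hernia surgery by hernia onset, and names the wrong variable for the safety outcomes

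*Protocol article*

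**What the plan says.** Outcomes {12} gives each secondary outcome nearly the same block of method text.

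- **Safety.** The list of wound complications ends "and need for mesh removal. Categorical variables (incisional hernia proportion in each group) will be described by absolute and relative frequencies". The next sentence says that "differences between groups will be calculated by chi-square test". No other method is given for this group of outcomes.
- **CT hernia.** The outcome is "Incidence of incisional hernia at 2 years post-transplantation by radiological diagnosis (CT"). It receives frequencies, a chi-square test, and a Kaplan-Meier and log-rank analysis of time to hernia onset.
- **Hernia surgery.** Here the parenthesis was adapted: "Categorical variables (incisional hernia surgery proportion in each group) will be described by absolute and relative frequencies". The time-to-event sentence was not, and it still refers to the onset of the hernia.

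Three other sections bear on this. The control-group closure technique is suture only, without mesh. Section {11b} lets the surgeon change the allocated closure with justification. The Discussion reports, for a transplant series in which mesh was used against compartment syndrome, "The mesh removal rate was 6% (8/134").

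**The concern.** These are analysis rules that the document states, not detail left to an analysis plan. Followed as written, they have four consequences.

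1. Mesh removal would be tested against an arm that has no mesh to remove. A p-value from that table says where meshes were placed, not how the two closures compare on safety.
2. The log-rank test reported under hernia surgery would be the primary outcome's log-rank test again, and nothing would be learned about time to repair.
3. Read literally, the safety outcomes would be summarised by the efficacy variable.
4. If CT is done only at 24 months, its time-to-onset analysis cannot describe onset.

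Low complication risk is part of the trial's stated aim, so a safety p-value without comparative meaning could mislead in either direction.

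**Working it through.** **The plan's own figure.** Inputs from Sample size {14}: 20% in controls, "a proportion of 5% in the intervention group (prophylactic mesh reinforcement placement"), alpha 0.05 (taken as two-sided), power 80%. With pooled variance and no continuity correction, the mean proportion is 0.125 and

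n = [1.960 × √(2 × 0.125 × 0.875) + 0.842 × √(0.20 × 0.80 + 0.05 × 0.95)]² / 0.15² = (0.917 + 0.383)² / 0.0225 ≈ 75.1, rounded up to 76.

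This agrees with the protocol: "the sample size per group was calculated at 76 patients". The points below do not touch it.

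**Mesh removal.** Let x be removals among 76 in the mesh arm, with 0 among 76 in controls. The uncorrected chi-square is

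152 × (76x)² / [76 × 76 × x × (152 − x)] = 152x / (152 − x).

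| x vs 0 | chi-square | p, uncorrected | p, continuity-corrected | p, Fisher |
|---|---|---|---|---|
| 0 | undefined | – | – | – |
| 3 | 456/149 = 3.06 | 0.080 | 0.244 | 0.245 |
| 4 | 608/148 = 4.11 | 0.043 | 0.128 | 0.120 |
| 5 | 760/147 = 5.17 | 0.023 | 0.069 | 0.058 |

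The uncorrected test therefore crosses 0.05 at x = 4. At the cited 6%, expected removals are 76 × 0.06 = 4.56, the smallest expected cell is 4.56 / 2 = 2.28, and P(x ≥ 4) under Binomial(76, 0.06) is 0.68.

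The 6% comes from a different indication, so a range is needed. Apart from 6%, these rates are assumptions:

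| Removal rate | P(uncorrected p < 0.05) | P(no removals, test undefined) |
|---|---|---|
| 0.6% | 0.001 | 0.63 |
| 1.5% | 0.03 | 0.32 |
| 3% | 0.19 | 0.10 |
| 6% | 0.68 | 0.009 |
| 10% | 0.95 | 0.0003 |

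Across this range the test moves from mostly undefined to nearly always significant, and nowhere does it compare treatments.

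For descriptive reporting, the exact (Clopper-Pearson) 95% limits for 5/76 are the 0.025 quantile of Beta(5, 72) and the 0.975 quantile of Beta(6, 71), that is 2.2% to 14.7%. This assumes that all 76 received mesh.

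**Hernia surgery.** The primary outcome and the surgery outcome carry the same time variable, time to hernia onset. Same event, same patients and same test give the same result. No arithmetic applies.

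**CT hernia.** Suppose every patient is scanned at one common date. With a single event time, the log-rank statistic equals the chi-square × (N − 1)/N. Take 4/76 against 15/76, close to the planned 5% and 20%:

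- chi-square = 152 × (4 × 61 − 72 × 15)² / (76 × 76 × 19 × 133) = 7.278, p = 0.0070
- log-rank = 7.278 × 151/152 = 7.230, p = 0.0072

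The two are practically the same test. If scan dates vary around 24 months, the log-rank ranks scan dates, which is not onset either.

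**The case against.** Most of the section works. The chi-square comparisons of seroma, wound infection, CT hernia and hernia surgery are sound two-group comparisons, and the general rule for categorical variables under Statistical methods {20a} makes the intended safety analysis clear despite the misplaced parenthesis. This stands: a reader might infer that the secondary analyses as a whole cannot give valid results, and the document does not support that.

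A reader might also infer that the mesh-removal test is significant by design. It is not. Three removals against none gives p of about 0.08, and even at 6% the test misses significance about one time in three. The chi-square sentence does not name mesh removal; it applies because it is the only comparison given for the whole safety list. Few readers would take removals against zero in patients without mesh as comparative evidence. This limits the harm but does not make the test meaningful.

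On CT, it is tempting to say that there is a single scan and that the log-rank is therefore invalid. The text fixes the outcome at 2 years, but the schedule figure is not shown, and Study setting {9} counts imaging done during follow-up as source data, so earlier CT diagnoses are possible. Even with one common date the log-rank is redundant and mislabelled, not numerically wrong. The CT point is therefore conditional.

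Nothing in the objection answers the wrong time variable for hernia surgery.

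**Conclusion.** The concern holds as a misspecification of some secondary analyses. Three parts need no inference about the schedule: mesh removal falls under a between-arm test with a control count of zero by construction (apart from allocation changes), hernia surgery is timed by the wrong event, and the safety parenthesis names the efficacy variable. The fourth, that the CT log-rank is redundant, holds only if CT is done at 24 months alone.

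The size of the mesh-removal problem depends on the removal rate. The figure of about 68% rests on the 6% from a different indication, on 76 per arm with no allocation changes, and on a chi-square without continuity correction. The conclusion that the test is not a treatment comparison depends on none of these figures. The corrections are worth making before the data are analysed, but they leave the primary endpoint, its analysis and the sample size as they are.

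**What to change.** Amend the secondary-outcome text as follows.

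1. **Mesh removal:** report n/N among patients who received mesh, with an exact 95% confidence interval and no between-arm test.
2. **Hernia surgery:** keep the chi-square on the proportion operated on, and define the Kaplan-Meier and log-rank variable as time from transplantation to hernia repair.
3. **Wound complications:** replace the hernia-proportion parenthesis with the proportion of patients having each named complication.
4. **CT hernia:** state when CT is done. If only at 24 months, analyse it as a 24-month proportion and drop the Kaplan-Meier and log-rank sentence.

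The cost is a wording change. It adds no outcome and no patients. Hernia surgery is already a trial outcome, so the one item to confirm is that the date of repair is recorded.
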